#### Team-level.

Inspectors from Company 1 occasionally and Company 3 always work in pairs, potentially causing spillover effects from the expected benefits of wearing a camera to colleagues. This is accounted for in the survey by asking whether the inspector worked alone or together with a colleague during the shift. For inspectors from the subcompany hired by Company 3 who always work with two or three colleagues, the randomization and treatment are allocated at the dyad-team-level to prevent spillover effects.

#### Instruction.

Implementing body-worn cameras requires clear instructions on their use, including when to activate them and how to inform passengers. Company 1 already has established routines, so staff will continue current practices. Companies 2 and 3 lack such routines; to ensure comparable implementation, they will adopt instructions similar to Company 1’s. However, some differences between companies are to be expected, particularly regarding the extent to which the presence of the cameras is announced to passengers. Since treatment fidelity regarding specific camera-use practices cannot be fully enforced across organizational contexts, we emphasize that the study’s strongest test is of the effect of the mere presence of a body-worn camera on the inspector’s uniform—the consistent element across all conditions—rather than how the camera is operated with slight differences between companies. As per the instructions, activation of the camera relies on the inspector’s assessment of a given situation, meaning that the camera only records when the inspector decides to record an incident.

### Camera visibility

In our pilot study, which included field observations of inspections *in situ*, we found that most passengers did not notice the camera on the inspector’s uniform during normal inspections. This may explain the lack of effect observed in prior studies: if passengers are unaware of the camera, it cannot influence their behavior. To investigate this further, we added a camera-with-badge condition to the experiment. In this condition, inspectors wear a clearly visible badge next to the camera, informing passengers that they may be recorded. The experiment therefore includes two treatment conditions—camera without badge and camera with badge—and one control condition without a camera or badge. The camera-with-badge condition is not applied in Company 1, as it already follows established camera-use practices that do not involve a badge. Thus, this three-arm design component is only examined in analyses excluding Company 1. The main two-arm analysis—comparing camera versus no camera—will be based on pooled data from all three companies.

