### Randomization

#### Camera use.

The study randomizes at the level of inspector shifts. Each inspector is assigned to wear a camera during a randomly selected 50% of their shifts over the study period (treatment) and to work without a camera during the remaining shifts (control). Four hours before each shift, participants receive an automated text message indicating whether they must wear a camera for that shift. If a shift starts before 12 pm, the text message is sent the evening before at 8 pm to avoid contacting participants between 8 pm and 8 am. The treatment message is sent within a time span that allows participants to have time to bring the camera to work while minimizing the risk that participants select routes based on whether they carry the camera or not (as some inspectors have freedom in choosing routes). While this design informs inspectors about their condition assignment in a timely manner, it does not eliminate the risk that inspectors adjust their inspection style and manner of coping with passenger conflicts in anticipation of their assigned condition. To assess this bias, we will examine whether outcomes vary across different notification times, on the assumption that shorter notice leaves less room for anticipatory adjustments.

The block-randomization design guarantees an even 50/50 split between treatment and control shifts for every participating inspector. Compared to the field trial by Ariel and colleagues [4], this approach offers key advantages: it ensures treatment and control observations are independent of inspector- or shift-specific characteristics, removes clustering by inspector, increases statistical power, and makes it more likely that randomization produces genuine *ceteris paribus* conditions [31,32]. Despite these strengths, this design carries a risk of contamination, as the same inspectors alternate between treatment and control shifts and may carry learned behaviors, fatigue effects, or other carry-over biases from one condition to the other [see, e.g., 33].

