### Data analyses

Our data analysis plan proceeds in three stages to comprehensively evaluate the impact of body-worn cameras. We will estimate the causal effect for two primary continuous outcomes: victimization and perceived safety. First, we will estimate the Intention-to-Treat (ITT) effect, which is the effect of the random *assignment* to carry a camera, regardless of actual use. This analysis preserves the benefits of the initial randomization. We will use an Ordinary Least Squares (OLS) regression model for this purpose:

$$Y_{i}=\beta_{\text{0}}+\;\beta_{\text{1}}Z_{i}+\epsilon_{i}$$

Here, Y_i is the outcome for inspector i, and Zi is a treatment indicator equal to 1 if the inspector was assigned to the camera group and 0 otherwise. The coefficient of interest, β1, represents the ITT effect.

Second, to account for potential non-compliance (i.e., inspectors not using their assigned cameras), we will estimate the Average Treatment Effect on the Treated (ATT). This represents the effect of actually using a camera for those who complied with the assignment. We will use the random assignment as an instrumental variable (IV) for reported camera use. The effect will be estimated using a Two-Stage Least Squares (2SLS) regression.

First Stage: Predict actual camera use based on the random assignment. Here, Di is an indicator for whether inspector i reported using the camera.

$$D_{i}=\gamma_{\text{0}}+\;\gamma_{\text{1}}Z_{i}+\nu_{i}$$

Second Stage: Use the predicted camera use from the first stage (D^i) to estimate the effect on the outcome. The coefficient δATT provides our estimate of the ATT.

$$Y_{i}=\lambda_{\text{0}}+\;\lambda_{\text{ATT}}{\hat{D}}_{i}+\eta_{i}$$

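### The main camera contrast mixes shifts with and without the recording badge, so it estimates camera with or without badge, not the camera's mere presence

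*Protocol article*

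**What the plan says.** The section on camera visibility sets out the arms: "The experiment therefore includes two treatment conditions—camera without badge and camera with badge—and one control condition without a camera or badge". Of the badge arm it says: "In this condition, inspectors wear a clearly visible badge next to the camera, informing passengers that they may be recorded". It also says that "The camera-with-badge condition is not applied in Company 1", so the three-arm comparison is confined to analyses without that company. The main analysis, however, covers everyone: "The main two-arm analysis—comparing camera versus no camera—will be based on pooled data from all three companies".

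The section on camera use gives the allocation: "Each inspector is assigned to wear a camera during a randomly selected 50% of their shifts". How camera shifts divide between badge and no badge is not given. In Data analyses, the intention-to-treat model has one regressor, Z, which "is a treatment indicator equal to 1 if the inspector was assigned to the camera group and 0 otherwise". There is no badge term, and nothing removes badge shifts.

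The Instruction section says what the result is meant to show: "we emphasize that the study’s strongest test is of the effect of the mere presence of a body-worn camera on the inspector’s uniform".

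**The concern.** The camera is common to all treated shifts, but the badge is not. Some treated shifts in Companies 2 and 3 carry a prominent notice that no control shift and no Company 1 shift carries. The single coefficient is therefore a weighted average of a camera-only effect and a camera-plus-badge effect. The weight is set by how many shifts each company happens to supply, not by any scientific choice.

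The article's own reasoning makes this matter. It added the badge because pilot observations suggested that most passengers did not notice the camera, and it argues that an unnoticed camera cannot change behaviour. A badge that works beside a camera that does not is thus a case the design anticipates. The reverse is also possible: the Introduction raises escalation through perceived power display, so a provocative badge could hide a camera benefit.

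At stake is what a company may conclude from the headline. A positive pooled result would not tell it whether a camera without the badge is enough.

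**Working it through.** **Inputs from the article**
- About 3,000 shifts, up to 60 inspectors, and 90% power at f² = 0.003 (Sample size and power analysis).
- Half of each inspector's shifts with a camera (Camera use): 1,500 camera and 1,500 control shifts.
- Companies 2 and 3 employ about 20 + 18 + 4 = 42 inspectors (Intervention setting), so at most 42/60 = 70% of participants.

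**Assumptions**
- Companies 2 and 3 supply a share s of shifts: 30%, 50% or 70%.
- Their camera shifts split evenly between badge and no badge.
- Two-sided 0.05 (alpha and sidedness are not stated), no clustering.

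**The plan's own figure.** With one predictor and N = 3,000, 90% power needs f² = 0.00286 one-sided or 0.0035 two-sided at 0.05. The one-sided value rounds to the stated 0.003. At exactly 0.003, two-sided power is 85%. With d = 2√f², the two-sided detectable effect is 2√0.0035 = 0.118.

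**What the pooled contrast estimates.** The badge share of camera shifts is w = s/2, so w = 0.15, 0.25 or 0.35.

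Pooled effect = (1 − w) × (camera-only effect) + w × (camera-plus-badge effect)

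**If only the badge works.** Set the camera-only effect to 0 and the camera-plus-badge effect to a reduction of d. The pooled effect is then w·d, its SE is √(2/1500) = 0.0365, and the chance of significance in that direction is Φ(w·d/0.0365 − 1.96).

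For d = 0.3:
- s = 30%: 0.15 × 0.3 = 0.045, Φ(−0.73) = 23%
- s = 50%: 0.25 × 0.3 = 0.075, Φ(0.09) = 54%
- s = 70%: 0.35 × 0.3 = 0.105, Φ(0.92) = 82%

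Other badge effects:

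| d | s = 30% | s = 50% | s = 70% |
|---|---|---|---|
| 0.2 | 13% | 28% | 48% |
| 0.3 | 23% | 54% | 82% |
| 0.4 | 38% | 78% | 97% |

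If Companies 2 and 3 instead used 1:1:1 allocation, w would be 0.18, 0.29 or 0.38, and d = 0.3 would give 32%, 64% or 86%.

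**Precision once the badge has its own term.** With company as a stratum, badge shifts carry no information on the camera-without-badge coefficient. Its information is the sum over strata of 1/(1/n_control + 1/n_camera only). At s = 70%:
- Company 1 (450 v 450): 225
- Companies 2 and 3 (1,050 v 525): 350
- SE = 1/√575 = 0.0417, and 0.0417/0.0365 = 1.14

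At s = 50%, SE = 1/√625 = 0.0400. At s = 30%, SE = 1/√675 = 0.0385. Multiplying by 1.96 + 1.28 gives detectable effects at 90% power of 0.125, 0.130 and 0.135 for s = 30%, 50% and 70%, against 0.118 for the pooled contrast. Power at d = 0.118 is 87%, 84% and 81%.

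**The case against.** The best defence is that camera with or without badge is a legitimate treatment. The article calls both camera conditions treatments and openly names the main contrast as camera versus no camera. The mere-presence sentence mainly sets presence against how the camera is operated, and the same section concedes that companies will differ in how far cameras are announced to passengers. This stands: the contrast is not invalid. What remains is that the badge is a deliberate extra arm within companies, not an incidental difference in practice, and the stated interpretation does not fit a mixture.

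Four stronger readings are tempting but not supported.

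- **That a badge-driven result is a false positive.** It is not, for the any-camera contrast. It misleads only if read as the effect of the camera alone.
- **That two-stage least squares fails outright.** If the exposure is the camera as deployed, badge included, assignment has no separate path through the badge. The exclusion restriction fails only if the exposure is the bare camera, which Data analyses does not say.
- **That 82% is the expected size.** It is an upper-end case under the even split. It needs all 42 employees of Companies 2 and 3 to enrol, although recruitment is voluntary. Company 1 has about 850 inspectors and started about four weeks earlier. The 0.3 SD is assumed, and clustering, including team-level allocation among Company 3's guards, would lower all the figures.
- **That Company 1 gives no notice and would necessarily be misinformed.** Its cameras carry a small recording sticker. Its shifts are randomised without a badge, and company is a listed moderator, though only for exploratory use.

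The secondary three-arm analysis does separate the badge, but without Company 1 and not for the main conclusion.

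**Conclusion.** The point holds as a mismatch between the main contrast and its stated interpretation, not as an invalid analysis. That badge shifts enter the camera arm is the plain reading of the camera-use, camera-visibility and data-analysis sections, although the article never says so outright. On that reading, the headline coefficient cannot be read as the effect of a camera's mere presence, and no stated analysis supplies the camera-without-badge effect over all three companies.

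The size depends on quantities the article does not give. Across the assumed shares and badge effects of 0.2 to 0.4 SD, a bare camera with no effect would still yield a significant main result between 13% and 97% of the time. With a small badge effect or few shifts from Companies 2 and 3, the risk is low.

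**What to change.** Keep all the data and fit the pooled intention-to-treat model with two assignment indicators and inspector (or company) effects:

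Y_is = a_i + b1·camera_is + b2·badge_is + e_is

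Here b1 is camera without badge versus none, across all three companies, and b2 is the badge increment, estimated in Companies 2 and 3. Report both beside the any-camera contrast, and attach the mere-presence interpretation only to b1. If the any-camera contrast stays the main one, define it in words as camera with or without badge.

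For two-stage least squares there are two workable choices:
- interpret the pooled estimate as the effect of the camera as deployed; or
- exclude badge-assigned shifts, with company as a stratum. The stratum is needed because, under the assumed split, the camera-to-control ratio becomes 1:2 in Companies 2 and 3 but stays 1:1 in Company 1.

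Use two exposures only if badge wearing is recorded. The shift-survey and moderator descriptions mention camera wearing and placement but not the badge.

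**Cost.** This is a wording and model change made before analysis, with no new randomisation. The price is precision: b1 has an SE up to about 14% larger (at a 70% share), and its detectable effect at 90% power rises from d = 0.118 to about 0.125–0.135.

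**Caveat.** Because of Company 1's sticker, even b1 is not a wholly notice-free camera effect, and the report should say so.

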### Survey

#### Baseline and background survey.

Before the intervention, inspectors complete a questionnaire assessing baseline self-perceived safety, attitudes toward body-worn cameras, trust in management, and sociodemographic information such as age, gender, ethnicity, and height and weight (for calculating body mass index, BMI). These data enable the examination of potential treatment effect heterogeneities—for example, whether women or individuals with lower BMIs experience greater benefits from body-worn cameras than colleagues with a more imposing physical presence. Identifying such heterogeneities will enhance the generalizability of the findings to other companies and contexts, providing more nuanced insights than a simple average treatment effect.

#### Shift survey.

At the end of each shift, inspectors receive an automated text message prompting them to complete a short questionnaire. This survey captures self-reported experiences of victimization (ranging from verbal condescension to physical aggression and violence), perceived safety, whether they worked with a colleague, and whether they wore a camera. The latter information enables estimation of the local average treatment effect among inspectors who comply with their randomly assigned treatment, using instrumental variable regression [34]. In the remainder of the paper, we refer to this questionnaire as “the survey.”

### Measures

#### Outcome measures.

The primary outcome measure is victimization, ranging from verbal offenses and harassment to physical violence. In the survey, participants report whether they experienced each of the following passenger behaviors 0, 1, 2, 3 or more times during the shift: behaved unpleasantly toward the inspector; were rude or condescending; raised their voice or cursed at the inspector; filmed the inspector with their phone against their will; came uncomfortably close in a threatening manner; touched or grabbed the inspector in an unpleasant way; acted aggressively or threateningly toward the inspector (e.g., banging on the window or threatening with an object); made verbal threats; spat at the inspector; or used physical violence (e.g., pushed, hit, or threw an object at the inspector). We will use Mokken scale methods to combine these observed measures into a single victimization scale and assess its measurement quality.

The victimization survey instrument is developed based on previous research on passenger aggression [35,36] and on Company 1’s incident records, which document the specific behaviors that occur in the registered victimization events. By grounding our measure in these context-specific descriptions rather than in abstract theoretical categories or instruments developed for other settings, we enhance the construct validity of our victimization measure.

The secondary outcome measure is self-perceived safety, based on inspectors’ assessments of how safe they felt during their most recent shift. It is measured on a five-point Likert scale ranging from not at all (1), to a low extent (2), to some extent (3), to a high extent (4), and to a very high extent (5), using a set of questions evaluating the extent to which the inspector felt unsafe, feared being assaulted, and avoided a passenger for their own safety during the shift. These items will be combined into an additive scale.

The primary and secondary outcome measures are based on inspectors’ subjective ratings of encountered passenger behavior and self-perceived safety during a shift. This reliance on self-report comes with the risk of expectancy bias, as inspectors may rate their experiences in accordance with treatment assignment—or conversely, may underreport benefits given some employees’ skepticism toward body-worn cameras. Blinding is not feasible, as inspectors are necessarily aware of whether they are wearing a camera—a common type of limitation in experimental social science research [37]. However, the parallel field observations provide some qualitative triangulation by offering independent insight into how staff-passenger encounters unfold.

#### Moderators.

We include a variety of moderators to explore heterogeneities in the camera’s effect on victimization. One group of moderators is measured in the initial baseline survey and includes the inspector’s gender, age, ethnicity, household status, work experience in the company, BMI, prior victimization, prior sick leave due to victimization, baseline sense of safety, and attitudes toward cameras and management. Another group of moderators includes company, shift start and end time, whether the inspector worked alone or in units for some or most of the shift, camera placement on the uniform, and whether a colleague was wearing a camera. All of these moderators are pre-treatment variables and are voluntarily provided by participants.

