### Intervention setting

The inclusion of three Danish traffic companies ensures variation in geography, demographics, and organizational contexts, including differences in vehicle types, inspector roles, tasks, and educational backgrounds. The companies also differ in their prior experience with body-worn cameras: one uses them routinely, another participated in the pilot phase of the current study, and the third has never used them. All three companies have in-vehicle surveillance cameras, although in one company these are no longer operational. In parts of the transport sector, body-worn cameras are met with mixed reactions—some inspectors welcome them as a security measure, while others express concern, particularly about surveillance and potential misuse of recordings by management. While the intervention will be implemented in the same overall manner across the three companies, certain elements will be adapted to account for differences in work practices and organizational structures, as outlined below.

Company 1 is Denmark’s largest train operator, employing approximately 850 inspectors who service regional and long-distance routes, as well as trains in the urban area of Copenhagen. The company implemented body-worn cameras on a voluntary basis in April 2023 and aims to broaden the use of cameras among employees, with 200 cameras distributed prior to the intervention and approximately 200 more deployed at its onset. The company participates in the study with the aim of reducing work-related victimization and giving non-wearers the opportunity to become familiar with wearing a camera in practice. The company already has formal guidelines for camera use that include an expectation to activate the camera in incidents where a conflict with a passenger escalates. Inspectors are not obliged to inform passengers that they are recording in case they think activation can escalate the incident. On each camera, there is a small sticker announcing potential recording. Inspectors who work in trains operating across the country work alone, except during evening shift after 10 pm, when they work in pairs for safety reasons. Inspectors patrolling the urban rail system work in pairs during evening shifts after 8 pm.

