Finally, to explore potential moderators, we will investigate treatment effect heterogeneity. We will use causal forests, a machine-learning method designed to estimate Conditional Average Treatment Effects (CATEs), defined as τ(X)=E[Y(1)−Y(0)|X = x]. This non-parametric approach will allow us to flexibly explore how the treatment effect varies across a range of pre-specified inspector characteristics (X) without being constrained by linear interaction terms. These explorative subgroup analyses will be conducted and disseminated with careful consideration of sensitive moderator variables such as BMI and ethnicity. Further, we acknowledge that our exploratory subgroup analyses imply an increased false-positive rate due to multiple comparisons [38], which will be addressed by interpreting statistical significance tests conservatively and clearly labeling these results as’exploratory’ in the Results section.

For all OLS and 2SLS regression models, we will calculate cluster-robust standard errors to account for the statistical dependence between inspectors working in dyads. Furthermore, as a robustness check, we will re-estimate our primary models including inspector fixed effects to control for any unobserved, time-invariant characteristics of the individuals.

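### The planned company comparison of the camera's effect is a comparison of different treatments, because the badge exists only in Companies 2 and 3 and the moderator analysis does not separate it

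*Protocol article*

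**What the plan says.** The Moderators section states its aim as "We include a variety of moderators to explore heterogeneities in the camera’s effect on victimization". After the baseline traits it adds shift-level and organisational variables: "Another group of moderators includes company, shift start and end time, whether the inspector worked alone or in units". The badge is not on the list.

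The Data analyses section estimates heterogeneity with causal forests. The estimand is the conditional mean of Y(1) − Y(0), a single binary contrast, used to "flexibly explore how the treatment effect varies across a range of pre-specified inspector characteristics".

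The Camera visibility section defines the conditions: "The experiment therefore includes two treatment conditions—camera without badge and camera with badge—and one control condition without a camera or badge". It then limits the badge: "The camera-with-badge condition is not applied in Company 1, as it already follows established camera-use practices that do not involve a badge". Of the three conditions it says that "this three-arm design component is only examined in analyses excluding Company 1", whereas "The main two-arm analysis—comparing camera versus no camera—will be based on pooled data from all three companies". Nothing says how badge shifts enter the moderator analysis.

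On Company 1's cameras, the Intervention setting section notes: "On each camera, there is a small sticker announcing potential recording".

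**The concern.** The content of the treated state depends on company. In Company 1 it is a camera with a small sticker. In Companies 2 and 3 it is a mixture of camera alone and camera plus a clearly visible badge. A company difference in a binary camera effect is therefore partly a difference in what was delivered. Adding the badge to the covariates does not repair this, because it is part of the treatment and never occurs on control shifts.

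The article's own reasoning makes a badge effect plausible. The pilot found that most passengers did not notice the camera, and the badge was added for that reason. If the badge works as hoped, it also creates an apparent company difference. The Objective section asks under which conditions cameras prevent victimization, and the baseline survey section intends heterogeneity results to support generalisation to other companies. A company contrast that carries a badge effect would mislead on both.

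**Working it through.** **Scale.** The only design figure is 90% power with 3,000 shifts at f² = 0.003. A one-predictor F test with noncentrality f² × N gives 85.1% at two-sided 5% and 91.2% at one-sided 5%. Two-sided 90% needs f² = 0.0035. The article states neither alpha nor sidedness, so the figure reproduces closely one-sided, or two-sided if 0.0035 was cut to 0.003. It is used here only as a yardstick: with a 1:1 split, d = 2 × √0.003 ≈ 0.11 SD.

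**Company contrast.** Let c be the camera's effect, equal in all companies; b the badge's added effect; and s the badge share of camera shifts in Companies 2 and 3.

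- Company 1: effect = c
- Companies 2 and 3: effect = (1 − s)c + s(c + b) = c + s·b
- Apparent company difference = s·b, with no true difference present

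The article does not state s. Taking one half, with a range of one third to two thirds:

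| b (SD) | s = 1/3 | s = 1/2 | s = 2/3 |
|---|---|---|---|
| 0.11 | 0.037 | 0.055 | 0.073 |
| 0.22 | 0.073 | 0.11 | 0.147 |

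At b = 0.22 and s = 1/2 the artefact equals the design effect.

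**How often it would show.** Simulation of a linear camera-by-company interaction: 60 inspectors × 50 shifts, independent errors with SD 1, the same camera effect everywhere, s = 1/2, 600 runs per setting, two-sided nominal 5%. Rejection rates:

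| b (SD) | 18 in Company 1, 42 in Companies 2 and 3 | 30 and 30 |
|---|---|---|
| 0.11 | 8.5% | 13% |
| 0.2 | 20% | 26% |
| 0.3 | 44.5% | 53% |
| 0.4 | 71% | 77% |

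With badge shifts removed, the mean interaction was 0.00 to two decimals or within 0.005 of it, and rejection was 3 to 6% throughout.

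**Team work, read without conditioning on company.** The distortion is s·b × (share of team shifts that come from Companies 2 and 3 − the same share among solo shifts). Per the Intervention setting section, Company 2 (about 20 inspectors) and four Company 3 inspectors work alone, and 18 Company 3 guards work in units. Company 1's paired share and its number of participants are not given. I assume equal shifts per inspector, and 18 to 40 of the 60 inspectors from Company 1.

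- Example with 18 from Company 1, none of their shifts paired: team 18/18 = 1.00; solo 24/42 = 0.571; 0.5 × 0.429 = 0.21 of b.
- Same staffing, 40% of Company 1 shifts paired: 18/25.2 = 0.714; 24/34.8 = 0.690; 0.5 × 0.025 ≈ 0.01 of b.
- Across the staffing mixes: 0.21 to 0.40 of b if Company 1 never pairs, 0.10 to 0.16 at 20% paired, 0.01 to 0.05 at 40% paired.

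For experience, attitudes and similar traits the article gives no distribution by company, so no figure can be derived.

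**The case against.** The strongest reply is that the article fixes pooling only for the main two-arm analysis and never says which shifts the forest uses; arm coding in an exploratory forest could be left to a fuller plan. That is fair as far as it goes. But the article does fix a binary estimand, names company as a moderator of the camera's effect, and separates the badge only where Company 1 is left out. A comparison that includes Company 1 then has nowhere else to put badge shifts.

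The article also labels subgroup results exploratory, lists differing camera practices as a limitation, and expects companies to differ in how cameras are announced. These points lower the stakes but do not remove the problem. The exploratory caution is directed at false positives from multiple comparisons, whereas this is a systematic shift. The stated limitation does not name the badge, which is an assigned and therefore separable condition. Company is indeed a bundle of many differences, but this one component can be taken out by design.

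Three stronger readings are tempting and are not supported:

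- A reader might infer that the forest will show cameras working in Companies 2 and 3 but not in Company 1. At increments of 0.11 to 0.2 SD the false signal reached significance in only about 8 to 26% of simulated runs.
- A reader might infer that team-work or inspector-type effects will be badge effects in disguise. The team-work distortion can be close to zero, the trait distortion cannot be computed, and company is itself a covariate, so the forest can condition on it.
- A reader might infer that the main result is biased. The pooled intention-to-treat estimate averages over the badge mixture but remains a valid comparison of assigned conditions.

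**Conclusion.** The point holds for the company moderator. For any non-zero badge effect, the company difference in a binary camera effect contains s·b: 0.055 to 0.11 SD for b of 0.11 to 0.22 SD at s = 1/2. This follows from the design; its size rests on the assumed badge share and increment. For moderators correlated with company, distortion is possible when they are read without conditioning on company, but its amount is not determined by the article. Within Companies 2 and 3 the badge is an experimental condition, so contrasts there are not confounded in this way. The consequence is confined to exploratory results, and the remedy is cheap enough that the change should be made.

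**What to change.** State that in the causal forest, and in any comparison of effects between companies, the treatment is held constant by one of two routes:

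1. Use only camera-without-badge and no-camera shifts; or
2. Fit a multi-arm causal forest with camera with badge as its own arm.

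Either way, read company differences from the no-badge contrast, since Company 1 has no badge shifts from which to estimate the other. Note Company 1's sticker when interpreting what difference remains.

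Cost: wording in the analysis plan. Route 1 drops the badge shifts from an exploratory analysis. If all 42 staff of Companies 2 and 3 take part, they supply 42/60 × 3,000 = 2,100 shifts; half are camera shifts (1,050), and half of those carry the badge under an even split, so about 525. It also changes the camera fraction in those companies from 1/2 to 525/(525 + 1,050) = 1/3, so the forest should be given company-specific assignment probabilities. Route 2 drops no shifts. The badge analysis already planned within Companies 2 and 3 needs no change.
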